### Randomization

The investigator shall convey the patient’s details to the central registration center via fax. After an eligibility check, the patients will be randomly assigned to receive EPA or placebo at the central registration center by a computer program using a minimization method, with stratification by age, gender, BMI, and institution. Thus, the patient assignment will be concealed from the investigator. The randomization center will allocate a numbered treatment pack to each patient, which will contain all the drugs or placebos needed to complete a course of the trial treatment for that patient.

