**Methods:**

This study is a multicenter, double-blind, placebo-controlled, randomized controlled trial to be conducted in patients with both colorectal ACF and colorectal polyps scheduled for polypectomy. Eligible patients shall be recruited for the study and the number of ACF in the rectum counted at the baseline colonoscopy. Then, the participants shall be allocated randomly to either one of two groups, the EPA group and the placebo group. Patients in the EPA group shall receive oral 900-mg EPA capsules thrice daily (total daily dose, 2.7 g per day), and those in the placebo group shall receive oral placebo capsules thrice daily. After one month’s treatment with EPA/placebo, colonoscopic examination and polypectomy will be performed to evaluate the formation of ACF, and the cell-proliferative activity and cell-apoptotic activity in normal colorectal mucosa and colorectal polyps.

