### Sample size estimation

In the chemoprevention trial conducted in FAP patients, the NSAID sulindac and selective cyclooxygenase-2 (COX-2) inhibitor celecoxib reduced polyposis of the retained rectum after colectomy with ileorectal anastamosis (IRA). As previously noted, EPA has a suppressive effect for polyp formation and proliferation of FAP [19]. From these reports, we estimated that NSAIDs and EPA may have equivalent effect on suppression of polyp formation and proliferation.

Based on the target in the NSAIDs chemoprevention study for ACF, Takayama et al. reported that sulindac administration at 300 mg/d for 2 months to post-polypectomy patients suppressed ACF formation, decreasing the number of ACF from 7.70 ± 4.04 (baseline) to 4.00 ± 2.95 (at 2 months, *p < 0.001*) [33]. Presuming EPA and sulindac may have equivalent effect in suppressing ACF formation, to detect the reduction in the number of ACFs in the EPA group using the Mann–Whitney U test with a two-sided significance level of 5% and a power of 80%, it was estimated that a sample size of 12 patients per group would be necessary. Assuming a 10% dropout rate, we propose to recruit 15 patients per group, that is, a total of 30 patients.

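### Minimisation leaves out the baseline rectal ACF count, which is known before allocation; with 15 per arm, chance can separate the arms at baseline by up to about three-quarters of the planned effect

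*Protocol article*

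**What the plan says.** The Randomization section of the protocol article assigns patients at the central registration center "by a computer program using a minimization method, with stratification by age, gender, BMI, and institution". The investigator faxes the patient's details and eligibility is checked before assignment. No other allocation factor is named.

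The order of events is in the Methods part of the Abstract: "the number of ACF in the rectum counted at the baseline colonoscopy. Then, the participants shall be allocated randomly to either one of two groups". Outcome measurements adds that the operators count ACF during the colonoscopy and that expert endoscopists later recount from the recording. An operator's count therefore exists at registration.

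Eligibility criteria require ACF to be present but give no lower or upper limit on their number. The only figures for spread are in Sample size estimation, from an earlier sulindac study: "decreasing the number of ACF from 7.70 ± 4.04 (baseline) to 4.00 ± 2.95 (at 2 months".

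Outcome measurements defines the primary endpoint as the change in ACF number at 1 month. Statistical analysis compares the number of ACF between groups by a Mann–Whitney U test and mentions no baseline adjustment.

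**The concern.** Minimisation is used in small trials to stop chance from separating the arms on variables that predict the outcome. Here it balances four variables that bear on the ACF count only indirectly. It omits the one measured on the same scale as the endpoint, in the same patients, shortly before allocation.

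With 30 patients and an open range of entry counts, the arms may start visibly apart. Because the stated test takes no account of baseline, a reader of the single result could not easily tell an EPA effect from a baseline difference, or a missing effect from one that the baseline had hidden. A change score does not remove the problem: patients with few ACF cannot fall far, and a higher starting arm tends to fall further by regression to the mean.

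**Working it through.** **Inputs**

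- Planned effect: 7.70 − 4.00 = 3.70 ACF (Sample size estimation).
- Baseline SD: 4.04, from the same cited study. That it applies to this trial is an assumption.
- Patients per arm: 15 recruited, 12 evaluable ("Assuming a 10% dropout rate, we propose to recruit 15 patients per group, that is, a total of 30 patients"; "it was estimated that a sample size of 12 patients per group would be necessary").
- Correlation between baseline and 1-month count: not given; taken as 0.3 to 0.9.

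**The plan's own sample size**

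The plan does not say which SD it used. With 2.95 and a two-sided 5% test at 80% power, n = 2 × (2.95 × (1.960 + 0.842) / 3.70)² = 9.98, so 10 per arm. A t-based calculation gives 12, as does dividing 9.98 by 0.864, the lower bound for the efficiency of the Mann–Whitney test. The stated 12 is thus reproducible with that SD. Allowing for 10% dropout, 12 / 0.9 = 13.3, so 14; the plan rounds up to 15. The present point does not dispute these figures.

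**Chance gap at baseline without the factor**

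SE of the difference in baseline means = SD × √(2/n); 95% limit = 1.96 × SE. Half the planned effect is 3.70 / 2 = 1.85.

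| Per arm | SE | 95% limit | Share of 3.70 | Chance of gap ≥ 1.85 |
|---|---|---|---|---|
| 15 | 4.04 × √(2/15) = 1.48 | 2.89 | 78% | 21% |
| 12 | 4.04 × √(2/12) = 1.65 | 3.23 | 87% | 26% |

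At 15 per arm the median gap is 0.6745 × 1.475 = 1.0 ACF (27% of the effect). The chance of a gap of 90% or more of the effect is 2.4%, and of the whole effect 1.2%. Simulated skewed counts (negative binomial, mean 7.7, SD 4.04) give almost the same 95% limits: 2.87 at 15 per arm and 3.25 at 12.

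The result depends on the SD. If the baseline SD were only 2.95, then SE = 2.95 × √(2/15) = 1.08, the 95% limit is 2.11 (57% of 3.70), and the chance of a gap of at least 1.85 is about 9%.

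**How much of a gap reaches the result**

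With equal SDs at both visits, a baseline gap g shifts the difference in 1-month counts by ρ × g and the difference in change by (ρ − 1) × g. For g = 2.89:

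| ρ | Shift in 1-month count | Shift in change |
|---|---|---|
| 0.3 | 0.87 | −2.02 |
| 0.5 | 1.45 | −1.45 |
| 0.7 | 2.02 | −0.87 |
| 0.9 | 2.60 | −0.29 |

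In simulated trials with no true effect and a Mann–Whitney test on the 1-month count, the false-positive rate was about 10%, 14% and 18% (ρ = 0.5, 0.7, 0.9) when the arms started at least 1.85 apart, and 3%, 2% and 1% otherwise. Weighted by 21% and 79%, these average 4.5%, 4.5% and 4.6%. The test therefore keeps its level overall, and the trouble is confined to the unlucky fifth of trials.

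**With the factor added**

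Minimisation was simulated for 30 patients with three two-level factors, a three-level institution and a two-level ACF split at the median; the other factors were assumed independent of ACF. The chance of a gap of at least 1.85 falls from about 21% to about 6% with deterministic minimisation, or about 10% with an 80% biased coin. The article does not say which is used.

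The SD of the treatment difference in change moves as follows:

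| ρ | Deterministic | 80% biased coin |
|---|---|---|
| 0.5 | 1.48 to 1.35 | 1.49 to 1.40 |
| 0.7 | 1.14 to 1.08 | 1.16 to 1.11 |
| 0.9 | 0.66 to 0.64 | 0.67 to 0.66 |

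The largest of these gains is (1.48 − 1.35) / 1.48 = 9%. For the raw 1-month count under the biased coin, the SD falls from about 1.48 to 1.41, 1.33 and 1.21.

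**The case against.** Minimising on four factors in a trial that calls itself preliminary is a valid design. Omitting a prognostic variable does not bias the allocation, and chance imbalance is part of the sampling error that the test already allows for. The choice of factors is partly a matter of judgement. On the endpoint as defined, change, the gain in SD is at most about 9%. An analysis adjusted for baseline would recover most of the precision without touching the allocation, and a statistical analysis plan that is not shown may contain one. The SD comes from one outside study of patients given a different drug, and the correlation is unknown.

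Most of this stands, and it limits the point to a cheap improvement in design. It does not remove it: the only test the article states is unadjusted, the count is available in time, and the factor makes large baseline gaps clearly rarer.

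A reader might also infer that the arms could easily start apart by nearly the whole planned effect. The figures do not support that at 15 per arm: the 95% limit is 78% of 3.70, and a gap of 90% or more has a 2.4% chance. Nor does a gap pass undiminished into the result. Only the fraction given by the correlation reaches the 1-month count, and for change the shift has the opposite sign.

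**Conclusion.** The point holds as a weakness of the allocation scheme, not as an error that invalidates the trial. If the cited SD of 4.04 applies, chance alone can separate the arms at baseline by up to about 2.9 ACF (95% limit) at 15 per arm, and by at least half the planned effect in about one trial in five. A gap of 2.9 would shift an unadjusted comparison of 1-month counts by about 0.9 to 2.6 ACF for correlations of 0.3 to 0.9. It would shift a change score by about 2.0 down to 0.3 ACF the other way.

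It would be wrong to conclude that the randomisation is biased or that the average type I error is inflated. The average power of the unadjusted test also barely moves when the factor is added. What is gained is a single small result that is less likely to be clouded by where the arms started. The sizes rest on the borrowed SD, the assumed correlations and equal SDs at both visits.

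**What to change.** Add the operator's baseline rectal ACF count as a fifth minimisation factor at two levels, reported on the registration fax. Fix the cut before the first allocation and give its basis. The article offers only a mean and SD from the cited study and no median, and the gains above assume a cut near the trial's true median. Use the operator's count for allocation, since the experts' recount from the recording comes later.

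The cost is one field on the form and one factor in the existing program, with no extra procedure or patient. Balance on age, gender, BMI and institution becomes slightly looser. The precision gain is small (about 0–9% in SD) if change is analysed, and also small if the analysis adjusts for baseline.

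For patients already allocated, the remaining protection is baseline adjustment in the primary analysis, specified before unblinding. Whether that analysis uses the count or the change should be settled at the same time, since Outcome measurements and Statistical analysis differ on it.

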### Drug supply

Enteric-coated EPA capsules (Ethyl icosapentate granular capsule®) and the placebo capsules (capric, caprylic and lauric acid medium-chain triglycerides) will be purchased from Nipro Pharma Corporation Co., Ltd, Osaka, Japan. All trial drugs will be packaged identically and identified only by number. Subjects will be instructed to take one package of the trial drug after every meal each day. Compliance will be monitored by counting the empty drug packages returned by the patients at polypectomy.

### Sample size estimation

In the chemoprevention trial conducted in FAP patients, the NSAID sulindac and selective cyclooxygenase-2 (COX-2) inhibitor celecoxib reduced polyposis of the retained rectum after colectomy with ileorectal anastamosis (IRA). As previously noted, EPA has a suppressive effect for polyp formation and proliferation of FAP [19]. From these reports, we estimated that NSAIDs and EPA may have equivalent effect on suppression of polyp formation and proliferation.

Based on the target in the NSAIDs chemoprevention study for ACF, Takayama et al. reported that sulindac administration at 300 mg/d for 2 months to post-polypectomy patients suppressed ACF formation, decreasing the number of ACF from 7.70 ± 4.04 (baseline) to 4.00 ± 2.95 (at 2 months, *p < 0.001*) [33]. Presuming EPA and sulindac may have equivalent effect in suppressing ACF formation, to detect the reduction in the number of ACFs in the EPA group using the Mann–Whitney U test with a two-sided significance level of 5% and a power of 80%, it was estimated that a sample size of 12 patients per group would be necessary. Assuming a 10% dropout rate, we propose to recruit 15 patients per group, that is, a total of 30 patients.

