### Statistical analysis

The number of ACFs in each group, the primary endpoint, will be compared between the EPA group and the placebo group by the Mann–Whitney U test. The safety, one of the secondary endpoints, will be compared by the chi-square test. The remaining results in the two groups will be compared by the Mann–Whitney U test or Student’s *t* test. A P values of < 0.05 will be regarded as indicative of significance. The analysis will be performed using SPSS, version 17.0 (SPSS Inc., Chicago, Il.).

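### The printed means and SDs do not reproduce 12 per group for 80% power in a two-sided 5% Mann–Whitney test; under usual assumptions about 15–17 are needed

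*Protocol article*

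**What the plan says.** Under Sample size estimation, the article takes its effect from a study of sulindac over two months, which it reports as "decreasing the number of ACF from 7.70 ± 4.04 (baseline) to 4.00 ± 2.95". It carries this over to EPA with the words "Presuming EPA and sulindac may have equivalent effect in suppressing ACF formation". For a Mann–Whitney U test it then claims the result "with a two-sided significance level of 5% and a power of 80%, it was estimated that a sample size of 12 patients per group". Recruitment is set by "Assuming a 10% dropout rate, we propose to recruit 15 patients per group, that is, a total of 30 patients".

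Under Statistical analysis, the number of ACFs in each group "will be compared between the EPA group and the placebo group by the Mann–Whitney U test". Under Outcome measurements, the primary endpoint is the change in ACF number after one month. The article gives no SD of change, no baseline/follow-up correlation, no assumption for the placebo arm and no distribution shape, and it does not say which SD entered the calculation.

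**The concern.** The paragraph names two means, two SDs, a test, a significance level, its sidedness and a power, so a reader can try to recover the stated 12. The usual calculations give a larger number.

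The figure supports the only primary comparison of a preliminary trial that, according to the Discussion, is meant to lead on to a long-term trial. If power is below the stated 80%, a true effect of the assumed size is missed more often than the one time in five that the article implies. A non-significant result would then be read with more confidence than the design supports.

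**Working it through.** **Inputs** (all from Sample size estimation): untreated state 7.70, SD 4.04; treated state 4.00, SD 2.95; two-sided 5%; 80% power; Mann–Whitney U; 12 per group, 15 recruited. Using them for a two-arm comparison treats the baseline value as the placebo arm, that is, it assumes no placebo change.

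**Standardised difference.** Difference = 7.70 − 4.00 = 3.70. SD = √[(4.04² + 2.95²)/2] = 3.54. d = 3.70/3.54 = 1.046.

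**Attempt to reproduce 12 per group as described (two-sided, both SDs)**

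| Method | Calculation | n per group | Power at 12 |
|---|---|---|---|
| Normal approximation | 2(1.960 + 0.842)²/1.046² = 14.3 | 15 | 72.7% |
| t test (noncentral t) | 15.4 | 16 | 68.8% |
| Mann–Whitney, normal-theory efficiency 0.955 | 15.4/0.955 = 16.1 | 17 | 66.6% |

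None gives 12. Noether's formula, a rougher approximation, gives 18.

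**Simulated two-sided Mann–Whitney power.** Means and SDs were matched to the printed values. Ranges cover the test with and without continuity correction.

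| Assumed shape | n = 12 | n = 13 | n = 14 | n = 15 |
|---|---|---|---|---|
| Normal | 64–67% | 68–70% | 72–73% | 75–77% |
| Negative binomial | 69–70% | 73–74% | 77–78% | 80–81% |
| Gamma | 72–75% | 76–78% | 80–81% | 82–84% |
| Lognormal | 82–84% | 85–86% | 88–89% | 90–91% |

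Simulated power first reaches 80% at 17 per group for normal data and at about 15–16 for negative-binomial counts.

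**Routes that do come out near 12**

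- One-sided 5%, both SDs: 2(1.645 + 0.842)²/1.046² = 11.3, so 12. Simulated one-sided Mann–Whitney power at 12 is 78% (normal) to about 81% (negative binomial). The article says two-sided.
- Two-sided, SD 2.95 in both arms: simulated exact Mann–Whitney power at 12 is 80%. This discards the 4.04 given for the untreated state. Using 4.04 in both arms gives about 54%.
- Two-sided, change score with an assumed correlation r of 0.7: SD of change in the treated arm = √(4.04² + 2.95² − 2 × 0.7 × 4.04 × 2.95) = 2.89. Mann–Whitney power at 12, normal data, is about 79–80% if the placebo SD is 4.04 at both visits, and about 82–84% if the SD of change is equal in both arms. At r = 0.5 the same two assumptions give about 58–60% and 63–65%; at r = 0.3, about 45–47% and 49–52%.

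**Dropout.** 12/0.9 = 13.3, so 14 would cover a 10% loss and the article takes 15. With 10% lost from 15, 15 × 0.9 = 13.5, so 13–14 remain evaluable.

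**The case against.** The strongest reply is that means and SDs alone do not fix Mann–Whitney power. The table bears this out: with the same four numbers, power at 12 runs from 64% to 84% depending on shape, and a lognormal shape exceeds 80%. So 65–70% must be presented as conditional on normal or negative-binomial counts. It does not rescue the figure, because the article states no skewed shape and even a gamma shape stays below 80% at 12.

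A second reply is that the primary endpoint is a change, and a change score with a correlation near 0.7 gives about 80% at 12 with a two-sided test. This also stands as a possibility. A reader might infer from the one-sided result that the authors ran a one-sided test, or that only an error can yield 12. The article supports neither inference, since at least three routes lead there and it does not show which was taken. But no correlation is given, the SDs printed are those of counts, and the Statistical analysis section speaks of the number of ACFs.

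Third, 15 are recruited rather than 12, so the practical shortfall is smaller than the figure at 12 suggests. With all 15 evaluable, negative-binomial counts give about 80%, and under a gamma shape 14 are enough. Going from 12 to 15 is not a mistake; it leaves one patient per group beyond the 14 required.

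Finally, the trial is preliminary, and the presumed equivalence of EPA and sulindac may be at least as uncertain as the power gap. That limits the consequences but does not make the stated figure follow from its inputs.

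**Conclusion.** Wrong as written. The printed inputs do not give 12 per group for 80% power in the two-sided Mann–Whitney test described. Under usual assumptions the requirement is 15 (normal approximation), 16 (t test) or about 15–17 (Mann–Whitney). At 12 evaluable per group, power is about 65–70% rather than 80%, so the chance of missing the assumed effect is about 30–35% rather than 20%. With the planned recruitment and dropout the gap narrows to power of about 68–78%.

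These figures assume normal to negative-binomial counts, both printed SDs, analysis of the counts and no change on placebo.

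A reader might go further and conclude that the trial's power is definitely below 70%, that the primary test is invalid or that more patients are required. The article does not support any of these: shape and endpoint scale are open, the test itself is not in question, and 15 per group come close to the target under some ordinary assumptions.

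**What to change.** Keep 30 patients and correct the sample size paragraph:

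- Restate the power of the two-sided 5% Mann–Whitney test for 7.70 ± 4.04 versus 4.00 ± 2.95 as about 68–78% with 13–14 evaluable per group and about 75–81% with all 15, for normal to negative-binomial counts. Declare the distribution shape as an assumption.
- State which SD was used in each arm.
- State whether the calculation and the primary analysis use the count or the change. If the change, give the assumed correlation or SD of change and recompute the power on that basis.
- State that the placebo arm is assumed not to change, since the effect is taken from a before–after fall within one treated group.

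If 12 came from another calculation, such as a change score, that calculation and its inputs should be printed instead. The change costs one reworded paragraph and a less favourable power statement. It needs no extra patients and alters nothing in the conduct of the trial.

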### Statistical analysis

The number of ACFs in each group, the primary endpoint, will be compared between the EPA group and the placebo group by the Mann–Whitney U test. The safety, one of the secondary endpoints, will be compared by the chi-square test. The remaining results in the two groups will be compared by the Mann–Whitney U test or Student’s *t* test. A P values of < 0.05 will be regarded as indicative of significance. The analysis will be performed using SPSS, version 17.0 (SPSS Inc., Chicago, Il.).

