### Intervention

All eligible patients will be allocated randomly to one of two groups, the EPA group and the placebo group. The endoscopists, doctors at the follow-up outpatient clinics, and patients will be blinded to the allocation. Patients in the EPA group shall receive oral 900-mg EPA capsules thrice daily (total daily dose, 2.7 g), and those in the placebo group shall receive oral placebo capsules thrice a day. At the end of 1 month of administration of EPA/placebo, polypectomy will be performed, and the changes in the number of ACF and in the mucosa will be evaluated.

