### Outcome measurements

The primary endpoint shall be the change in the number of colorectal ACF after 1-months’s intervention. The endoscopic examinations and polypectomies will be performed using Olympus colonoscopes (model H260AZI). Bowel preparation prior to the colonoscopic procedures will be as described [33,34]. At the time of the first colonoscopy, the endoscope shall be inserted into the cecum, and the entire colorectum will be carefully observed as the endoscope is pulled back. If any polyps are detected, biopsy will be performed. Furthermore, colonic epithelial samples will be obtained. The number of rectal ACF will be counted with a magnifying endoscope, as described [25,33]. At the end of 1 month of administration of EPA/placebo, the same endoscopists will perform the polypectomy and counting of the ACF. All procedures will be recorded on DVD, and all the ACF will be photographed. The number of ACF in each patient will first be counted by the operators during the performance of the colonoscopy. To further ensure validity, the number of ACF will be counted again through observation of the recorded DVD by 3 blinded expert endoscopists ([name], [name], and [name]). If these expert endoscopists judge the colonoscopic examination as having been inadequate in any case, that case will be excluded.

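### The primary variable is the change in ACF number in one section and the number of ACF in another, and neither form uses the baseline count as a covariate

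*Protocol article*

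**What the plan says.** - **Outcome measurements** defines the endpoint: "The primary endpoint shall be the change in the number of colorectal ACF after 1-months’s intervention".
- **Intervention** agrees with that. After one month of treatment, "the changes in the number of ACF and in the mucosa will be evaluated".
- **Statistical analysis** attaches the same label to another variable: "The number of ACFs in each group, the primary endpoint, will be compared between the EPA group and the placebo group". The test is the Mann–Whitney U test, which has no covariate term. The sentence gives no visit and does not mention change or baseline.
- **Sample size estimation** does not settle the matter. It speaks of a reduction in the EPA group and takes its effect from a before/after contrast in a sulindac study, "decreasing the number of ACF from 7.70 ± 4.04 (baseline) to 4.00 ± 2.95 (at 2 months". It gives single-visit means and SDs only, with no SD of the change and no correlation between visits.
- **Baseline** is available for every patient. The abstract has "the number of ACF in the rectum counted at the baseline colonoscopy", followed by allocation. Under Randomization, the minimisation factors are age, gender, BMI and institution, so baseline ACF count is not balanced by design.
- **Site label.** The endpoint is called colorectal, but what is counted is rectal: "The number of rectal ACF will be counted with a magnifying endoscope".

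**The concern.** The number at 1 month and the change from baseline have different variances and respond differently to chance differences at baseline. In a 30-patient trial they can easily fall on opposite sides of 0.05. As written, an analyst could report either one and point to a sentence in the article that calls it the primary endpoint. If that choice were made after the data were seen, the 5% error rate would not hold. In addition, a count taken before allocation, and probably related to the outcome, is not used as a covariate under either reading.

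**Working it through.** **Inputs from the article (Sample size estimation).** Means 7.70 and 4.00, so δ = 3.70. SDs 4.04 and 2.95, pooled √[(4.04² + 2.95²)/2] = 3.54. Two-sided 5%, 80% power, 12 per group, 15 after the dropout allowance.

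**Assumptions.** Placebo stays at 7.70 ± 4.04 and EPA reaches 4.00 ± 2.95. The baseline/1-month correlation ρ is not in the article, so a range is shown.

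**Step 1: the plan's own figure.** n = 2[σ(1.96 + 0.84)/δ]² per group.
- With σ = 2.95 this gives about 10. The t-test solution is 11.03, and dividing by the Mann–Whitney efficiency 0.955 gives 11.55, so 12.
- With σ = 3.54 it gives 15, or 16.1 after the same two steps. A one-sided test with σ = 3.54 also gives 12.

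The stated 12 can therefore be reached from single-visit SDs. No SD of change enters, so the calculation does not show that the change was the variable powered.

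**Step 2: how the variables differ.** With SD 3.54 at both visits:
- number: SD = 3.54
- change: SD = 3.54·√[2(1 − ρ)]
- baseline-adjusted: SD = 3.54·√(1 − ρ²)

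Power = Φ[δ/(SD·√(2/n)) − 1.96], at n = 12 per group:

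| ρ | SD of change | SD adjusted | Power, number | Power, change | Power, adjusted |
|---|---|---|---|---|---|
| 0 | 5.00 | 3.54 | 73% | 44% | 73% |
| 0.3 | 4.19 | 3.37 | 73% | 58% | 77% |
| 0.5 | 3.54 | 3.06 | 73% | 73% | 84% |
| 0.7 | 2.74 | 2.53 | 73% | 91% | 95% |

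With equal SDs the change beats the number only above ρ = 0.5. If the SD falls from 4.04 to 2.95 in both arms, the crossing point is 4.04/(2 × 2.95) = 0.68.

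**Step 3: simulation with counts.** Correlated negative binomial counts with the means and SDs above, 15 per arm, ρ on the latent scale:

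| ρ | Mann–Whitney, number | Mann–Whitney, change | ANCOVA | ANCOVA minus number | ANCOVA minus change |
|---|---|---|---|---|---|
| 0 | 80% | 42% | 80% | 0 | 38 |
| 0.3 | 80% | 54% | 81% | 1 | 27 |
| 0.5 | 80% | 71% | 88% | 8 | 17 |
| 0.7 | 80% | 89% | 96% | 16 | 7 |

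At 12 per arm the gain over the number is about 10 points at ρ = 0.5 (69% to 79%) and about 21 at 0.7 (69% to 90%). In a bivariate normal version at 15 per arm, rank-based ANCOVA is 2 to 3 points below ANCOVA (79%, 85%, 95% against 82%, 88%, 97% at ρ = 0.3, 0.5, 0.7).

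**Step 4: what the ambiguity costs.** Under the assumed effect, the two Mann–Whitney tests disagree on significance in about 25–43% of trials over ρ = 0 to 0.7. The normal version gives 35%, 32% and 27% at ρ = 0.3, 0.5 and 0.7. With no drug effect, declaring success if either test is significant rejects in about 6–9% of trials. Each test alone, and ANCOVA, stays near 5%.

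**Step 5: baseline imbalance.** The standard error of the baseline difference is 4.04·√(2/15) = 1.48 ACF, and 1.48/3.70 = 40% of the target effect. A difference of 1.5 or more in either direction has a 31% chance (1.5/1.48 ≈ 1.02 standard errors). With equal SDs only the fraction ρ of it carries into the 1-month comparison: at ρ = 0.5, 1.5 × 0.5 = 0.75 ACF; at ρ = 0, none.

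**The case against.** The strongest reply is that the Statistical analysis sentence is shorthand. It labels its variable the primary endpoint, which Outcome measurements defines as the change, and Intervention also speaks of changes. That is plausible. A reader might infer that the plan commits to a raw 1-month count, but the text never says so. What stands is that the article does not settle which variable is tested.

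A reader might also infer three stronger things that the article does not support.

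- **That the mismatch wastes power.** No correlation is given. Against the unadjusted number, baseline adjustment gains almost nothing at 0.3 or below. Against the change score, testing the number gains power at low correlation, so simply aligning the test with the endpoint as defined could lose power.
- **That chance imbalance biases the result or manufactures an effect.** Randomisation makes the comparison of 1-month counts valid, and its error rate already includes chance imbalance. The 40% in Step 5 describes the baseline difference, not the error in the treatment effect.
- **That leaving out a covariate is itself an error.** A Mann–Whitney test is a legitimate choice, and covariates are commonly left to an analysis plan that is not shown here.

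The rectal/colorectal wording is a matter of labelling. The article is clear that the rectum is where ACF are counted.

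None of this removes the contradiction. Two sentences in the same article give the primary label to different variables, and a document that is not shown cannot make both correct.

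**Conclusion.** The point holds as an inconsistency in the primary variable, with baseline adjustment as the sensible way to resolve it. Its cost is about 25–43% disagreement between the two readings at 15 per arm under the assumed effect, and a false-positive rate of about 6–9% if the choice follows the data. These figures rest on the sulindac means and SDs, a placebo arm that does not change, and assumed correlations from 0 to 0.7.

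The efficiency argument is conditional. Over the unadjusted number, the gain is about none at correlations of 0 to 0.3, about 8–10 points at 0.5 and about 15–20 at 0.7. Over the change score it is larger at low correlation: 38 points at 0, falling to 7 at 0.7. At no correlation examined did adjustment lose more than simulation error. It is therefore a safe choice when the correlation is unknown, but its absence does not make the planned test invalid.

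**What to change.** Before unblinding, state one primary analysis in the same words under Outcome measurements, Sample size estimation and Statistical analysis: the rectal ACF count at 1 month, compared between arms with the baseline rectal count as covariate. Use rank-based ANCOVA to stay non-parametric, or ANCOVA reporting the adjusted difference with its 95% confidence interval. Keep the Mann–Whitney test as a sensitivity analysis, on a variable named in advance. Under Sample size estimation, also give the SD and the baseline/1-month correlation assumed.

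Keeping the change as the sole primary variable would also end the ambiguity, but at low correlation it gives up power, as the tables show.

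The cost is wording and one degree of freedom. No new data or visits are needed, because the baseline count is already taken before allocation.
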